**Fig. 1 Fig1:**
[figure not shown]
Study Diagram and Group Allocation of Patients

Whilst these are indicative of the possibility that the patient may have some form of dementia/cognitive impairment, it is often not possible to obtain confirmative evidence until at least 1-month post-op. Using the AMT or 4AT scores allows us to allocate patients to a group at the recruitment stage. However, we will also take into account any subsequent evidence of dementia in the analysis, by gaining permission/consent to access a patient’s notes and/or where possible, a consented suitable informant (someone who has contact with the patient at least once a month face-to-face or via telephone) via the Informant Questionnaire for Cognitive Decline in the Elderly (IQCODE). This will inform what final group cohort the patient is then allocated to. In the absence of a formal documented diagnosis of dementia and in accordance with previous research [20, 21], patients with an associated suitable informant IQCODE score of 3.31 and above will be assessed as having sufficient evidence of dementia to be allocated to the corresponding group cohort.

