### Recruiting patients with fluctuating and/or reduced capacity in England and Scotland

The aims of this study are incompatible with only enrolling patients with minimal or mild confusion. It is important to ensure findings are broadly applicable to those patients with a pre-existing diagnosis or evidence of dementia. Participants who lack capacity to give informed consent must therefore be included. In this situation, the patient’s agreement to participate will still be obtained to their best level of understanding (in line with legislative frameworks in England [23] and Scotland [24]). Where patients in England are assessed as lacking capacity to make a decision regarding their initial or continued involvement with the study, we will seek a personal or nominated consultee agreements [25]. In Scottish study sites where a patient is assessed not to have capacity, a legal representative will be sought and asked to consent in relation to the patient’s participation in the research [26].

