#### Post-op 1-month (± 5 days)

The 1-month post-op period will provide clinical teams with an opportunity to contact the patient’s General Practitioner (GP) and review their case notes to assess if the patient has a pre-existing documented diagnosis of dementia, as well as record some additional clinical measures and test results. If the patient has an eligible suitable informant, clinical teams will also use this time to complete IQCODE assessment if they have not already done so.

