There will be a number of patients from Group 1 (Pre-operative acute hip fracture patients with confusion) for whom we cannot find evidence of dementia at 1-month post-op. The samples and data from this (confused, non-dementia) group will be deposited into a biobank at the Norwich Biorepository, for use in future research studies. In cases where patients were initially in Group 2 (Pre-operative acute hip fracture patients without confusion) but where evidence of dementia is available at 1 month post-op, we will reallocate these patients to the dementia patient group.

Comparable data will also be provided from a third group (Oslo Cohort) of 200 ‘stable’ patients living with a confirmed dementia diagnosis, taken from existing memory clinic data (Norwegian Registry of Persons with Cognitive Symptoms (NorCog) (Reference: S-08143a and 2017/371). Samples for this group are already available, as lumbar puncture is part of the diagnostic workup of patients included in the Norcog registry (Reference: S-08143a). These samples were analysed in 2017 at Sahlgrenska for the following: Aβ38, Aβ40, Aβ42, 10xAb42/Ab40, YKL-40, IL-1β, IL-6, IL-8, TNF-α, G36-NG2. The respective regional committee responsible have already provided permission to compare these results with those gathered in the present study.

Thus, we shall assemble data from 3 groups (hip fracture and dementia, hip fracture and non-dementia, stable and dementia), each with an expected 200 subjects. Please (see Fig. 1: Study diagram and group allocation of patients).

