#### Primary hypothesis

We will address the primary hypothesis, that systemic inflammation arising from hip fracture leads to an acute brain injury, by comparing the level of inflammatory and neuronal injury CSF and blood markers between the three groups defined above. Accordingly, we predict raised inflammatory and injury markers for the confirmed dementia-hip fracture group compared to the medically stable dementia group (Oslo cohort) and compared to the non-dementia hip fracture group.

Each of the markers will be compared across groups using a general linear model with the marker as the dependent variable (i.e. a separate model for each biomarker). The initial model will simply include group as an explanatory factor. A further model will then be constructed, including potential confounding variables, such as age, to provide an adjusted between group mean difference (comparing fracture patients with dementia to fracture patients without and fracture patients with dementia to stable dementia patients), together with 95% confidence intervals and significance test. In the event of the residuals for these models not appearing normally distributed, an appropriate transformation will be applied, such as a logarithmic transformation. We also predict that patients with dementia will have significantly worse cognitive and functional informant-based scores. A similar analysis will be conducted with cognitive and functional scores as the dependent variable.

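### Oslo CSF was taken at diagnostic workup while the fracture-dementia group has no stage limit, so a difference in disease stage may be read as a fracture effect

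*Protocol article*

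**What the plan says.** **Comparator.** Under Sample size, the third group is 200 people with a confirmed dementia diagnosis, "taken from existing memory clinic data". On their CSF the protocol states: "Samples for this group are already available, as lumbar puncture is part of the diagnostic workup of patients included in the Norcog registry". The Background calls this cohort stable because its members have had no systemic inflammatory response from an injury. It does not mention stage of dementia.

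**Fracture-dementia group.** The eligibility criteria under Participants set no limit on severity or duration of dementia. The section on reduced capacity states "The aims of this study are incompatible with only enrolling patients with minimal or mild confusion" and "Participants who lack capacity to give informed consent must therefore be included". At 1 month, teams contact the GP and review the notes to "assess if the patient has a pre-existing documented diagnosis of dementia". Without a documented diagnosis, an informant "IQCODE score of 3.31 and above will be assessed as having sufficient evidence of dementia" (Design). Patients who screen as non-confused but later show evidence of dementia are moved into this group (Sample size).

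**Use of the contrast.** Under Primary hypothesis, the protocol tests whether inflammation from the fracture injures the brain by comparing markers across the groups: "we predict raised inflammatory and injury markers for the confirmed dementia-hip fracture group compared to the medically stable dementia group (Oslo cohort"). An adjusted model adds potential confounders, with age as the only named example.

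**The concern.** To attribute a difference between the fracture-dementia and Oslo groups to the fracture, the two should be alike in everything else that moves the markers. Stage of dementia is an obvious candidate. One group was sampled around the time of diagnosis. The other is a mix of long-diagnosed, recently diagnosed and undiagnosed patients. This is a mismatch between incident and prevalent disease, and it would remain even if both cohorts used the same definition of dementia.

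The other primary contrast does not help. Everyone in it has a fracture, so it cannot isolate a fracture effect, and more advanced dementia could shift markers there too. The causal reading therefore rests on the Oslo contrast, where a stage difference is a rival explanation.

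**Working it through.** **1. Is stage at sampling comparable?**

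| | Oslo | Fracture with dementia |
|---|---|---|
| When CSF was taken | Diagnostic workup | Day of hip surgery |
| Time since diagnosis | About zero | Any, or no diagnosis (IQCODE only) |
| Limit on stage | None described | None |
| Matching on stage | None described | None described |

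**2. Is there a stage measure that could link the cohorts?**

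- AMT or 4AT: taken in the acute episode. The Design section itself says that confusion may be an acute reaction to the fracture.
- MMSE-2:SV: taken about 48 h after surgery, at latest 60 h (Table 1). It is also an acute-episode score.
- IQCODE: the one pre-fracture measure. An informant is wanted but not required (Participants), and no Oslo counterpart is described.
- Record review at 1 month: the article mentions whether a diagnosis exists, plus further unspecified measures and results.

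So no pre-fracture stage measure available in both cohorts is described.

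**3. Which markers are affected?** Sample size lists the Oslo results as Aβ38, Aβ40, Aβ42, their ratio, YKL-40, IL-1β, IL-6, IL-8, TNF-α and G36-NG2. T-tau, P-tau, NfL, synaptotagmin and SNAP-25 are not on that list. On the list as given, the point bears on the Aβ markers, YKL-40, the cytokines and G36-NG2.

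**4. The plan's own power figure.** Inputs from Sample size: 200 per group, 0.33 SD, two-sided 5%, 90% power.

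- SE of a difference in SD units = √(2/200) = 0.10.
- Power at 0.33 SD = Φ(0.33/0.10 − 1.96) = Φ(1.34) = 0.910.
- Difference detectable with 90% power = (1.960 + 1.282) × 0.10 = 0.324 SD.
- With R² = 0.25: 0.324/√0.75 = 0.374, against the stated figure of about 0.37.

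The stated figures reproduce, so there is no arithmetic error.

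**5. What would a stage-only shift do?** The protocol gives no stage effect, so the shift b (in SD) is an assumption. With no fracture effect:

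P(significant) = 1 − Φ(1.96 − b/0.10) + Φ(−1.96 − b/0.10)

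| b (assumed) | Normal approximation | Noncentral t |
|---|---|---|
| 0.05 | 0.079 | 0.079 |
| 0.10 | 0.170 | 0.169 |
| 0.15 | 0.323 | 0.322 |
| 0.20 | 0.516 | 0.514 |
| 0.33 | 0.910 | 0.909 |

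For b = 0.10: 1 − Φ(0.96) + Φ(−2.96) = 0.1685 + 0.0015 = 0.170. The formula is symmetric in b, so a shift the other way gives the same rate of significant results. A larger sample does not remove the bias.

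**The case against.** The case against has five strands.

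- **Confusion is not stage.** The passage on capacity concerns acute confusion, and the protocol recognises that capacity may be regained, for example after delirium. A reader might infer from it that the groups differ in stage by construction. It does not show that.
- **Direction is open.** A reader might also infer that the fracture group is more advanced, so that the bias favours the predicted result. IQCODE-only cases and patients reallocated from the non-confused group could be at or before the Oslo stage.
- **Adjustment is not ruled out.** The confounder list is open-ended, details are left to an SAP that is not shown, and IQCODE does refer to pre-fracture cognition. To say that adjustment cannot remove the difference goes too far.
- **The record review may already capture more.** An article does not list form fields, and this one mentions further measures. That the diagnosis date goes unrecorded cannot be concluded.
- **The illustration is generic.** The shifts are assumed and would fit any confounder in a comparison of 200 with 200. Nor does the protocol say that the markers on the Oslo list change with stage.

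All five stand as limits on the claim. They do not remove its core. Oslo was sampled at workup, the fracture group has no stage limit, and the difference is to be attributed to the fracture. An SAP can adjust only for what was measured, and no common pre-fracture stage measure is described. The protocol's remark that pre-fracture data cannot be collected directly explains the difficulty but does not resolve it.

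**Conclusion.** The point holds as a possible confounding of the fracture-dementia versus Oslo contrast by stage at sampling. This is a matter of design, not a missing covariate list. The protocol establishes neither that a stage difference exists, nor its size, nor its direction. If one does exist, a modest shift is enough to matter: 0.10 to 0.20 SD would raise the chance of a significant result per marker from 5% to between about 17% and 51% with no fracture effect. Those figures rest on assumed shifts, 200 per group and the unadjusted comparison. The neuronal injury markers absent from the Oslo list should not be cited as examples for this contrast.

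**What to change.** - **Data.** In the planned GP and case-note review, record the date of dementia diagnosis and any last pre-fracture severity statement or cognitive score, if not already captured.
- **Sensitivity analysis.** Repeat the Oslo contrast with only those fracture patients diagnosed within about 12 months before fracture.
- **Supportive model.** Add time since diagnosis, with Oslo at about zero. Do not make the extrapolated value at zero years the main estimate.
- **IQCODE-only patients.** Report them as a separate stratum. They have no diagnosis date, and undiagnosed does not mean early.
- **Interpretation.** Judge consistency by estimates and confidence intervals, not by significance in the subset. If 50 fracture patients remained (an assumption), the SE against 200 would be √(1/50 + 1/200) = 0.158. Power at 0.33 SD would then be Φ(0.33/0.158 − 1.96), about 55%, so a true effect would often miss significance. If the estimate changes materially, describe the contrast as associational.

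The cost is one or two fields in an existing review and two additional analyses, with no new patients or samples. The restricted analysis will have wider intervals, and diagnosis date is an imperfect proxy for stage.

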### Analysis

All analyses will be conducted according to a detailed Statistical Analysis Plan (SAP), agreed by the Study Management Group (SMG) prior to analysis. A summary of the main analyses are given below however:

#### Primary hypothesis

We will address the primary hypothesis, that systemic inflammation arising from hip fracture leads to an acute brain injury, by comparing the level of inflammatory and neuronal injury CSF and blood markers between the three groups defined above. Accordingly, we predict raised inflammatory and injury markers for the confirmed dementia-hip fracture group compared to the medically stable dementia group (Oslo cohort) and compared to the non-dementia hip fracture group.

Each of the markers will be compared across groups using a general linear model with the marker as the dependent variable (i.e. a separate model for each biomarker). The initial model will simply include group as an explanatory factor. A further model will then be constructed, including potential confounding variables, such as age, to provide an adjusted between group mean difference (comparing fracture patients with dementia to fracture patients without and fracture patients with dementia to stable dementia patients), together with 95% confidence intervals and significance test. In the event of the residuals for these models not appearing normally distributed, an appropriate transformation will be applied, such as a logarithmic transformation. We also predict that patients with dementia will have significantly worse cognitive and functional informant-based scores. A similar analysis will be conducted with cognitive and functional scores as the dependent variable.

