Previous studies in older people with acute systemic inflammation have been limited by small sample sizes, the lack of adequate control groups and, in particular, have not assessed the impact of inflammation on recently emerging biomarkers of new brain injury [13].

One of the other difficulties encountered by research in this area is that hip fracture is an emergency and studies cannot directly collect pre-fracture data. However, well-validated methods for the assessment of pre-fracture cognitive ability are available. The Informant Questionnaire for Cognitive Decline in the Elderly (IQCODE [14] is one example widely-used clinically and for research purposes.

In the United Kingdom (UK) a significant proportion of hip fracture patients undergo surgery within spinal anaesthesia [15]. This routine clinical procedure involves inserting a needle into the patient’s spinal space (subarachnoid space) and injecting anaesthetic into the CSF. In this way, CSF can be collected just before the initiation of anaesthesia, using the same needle that will be used to administer the anaesthetic agent. This means that older patients undergoing emergency hip fracture repair surgery are a suitable group in which to measure systemic inflammation, brain inflammation and CSF markers of brain injury.

The impact of Acute SystematiC inflammation upon cerebRospinal fluId and blood BiomarkErs of brain inflammation and injury in Dementia: a study in acute hip fracture patients (ASCRIBED) will use the opportunity provided by hip fracture operations undertaken via spinal anaesthesia to investigate the impact of acute systematic inflammation upon CSF and blood biomarkers of brain inflammation and neuronal injury and on the exacerbation of dementia. We will collect samples from patients with and without dementia who are suffering a systematic inflammatory response (the ASCRIBED cohort). We will compare ASCRIBED’s ‘unstable’ groups (termed as to refer to the inflammatory response) with an existing cohort of patients living with dementia who have not experienced a systemic inflammatory response from an injury (henceforth known as the ‘Oslo’ cohort). The Oslo cohort will therefore provide ‘stable’ comparators. The study will shed light on the ability of acute inflammatory trauma to produce new brain injury in a vulnerable older population. The findings will then inform the search for new treatments targeting inflammation in dementia.

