### Sample size

We will recruit 200 patients with dementia and hip fracture; and 200 patients without dementia but who have experienced a hip fracture. This sample size is pragmatically based upon what would appear to be achievable in the time available and with consideration of likely statistical power. Without adjustment, a sample size of 200 subjects per group will provide statistical power of 90% to detect a mean between group mean differences of 0.33 standard deviations in any outcome variable using a two-sided significance level of 5%. Assuming confounding variables entered into a General Linear Model ‘explain’ no more than 25% of the total variation (i.e. the co-efficient of determination, R2, is less than 0.25), then this sample size should provide 90%. Power to detect an ‘adjusted’ mean difference of around 0.37 residual standard deviations [27]. In either case, this would be deemed a relatively small effect to be detected with high probability.

Data will be collected initially from two different groups:
Group 1: Pre-operative acute hip fracture patients with confusion;Group 2: Pre-operative acute hip fracture patients without confusion.

In respect of Group 1 (those with confusion), the AMT (England) and 4AT (Scotland) score indicate that a patient may be living with dementia. However, this may not be confirmed until 1-month post-op when reviewing the patient’s case notes, contacting their GP or reviewing their relevant Suitable Informant’s IQCODE Scores. Based on prior research, we anticipate that up to 50% of patients who have an AMT score of 8 or less (England) or 4AT score of 1 or above (Scotland) will have dementia (diagnosed or undiagnosed/vectored) [22]. Therefore, up to 400 may need to be recruited to this group. Recruitment will be monitored and stopped for Group 1 as soon as we receive 200 patients with confirmed dementia required for the study.

We will also collect data from patients without confusion (Group 2), who are unlikely to be confirmed with dementia at 1-month post-op. These patients will be included in the non-dementia group. Again, recruitment will be monitored and stopped from this group once 200 non-dementia patients have been included. The number required from this group will be dependent upon the non-dementia confirmation rate for this group.

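### With one residual variance across three groups, at least one primary contrast is miscalibrated if spreads differ, and the stated normality check does not reliably prevent it

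*Protocol article*

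**What the plan says.** The Primary hypothesis section of the protocol article sets the method: "Each of the markers will be compared across groups using a general linear model with the marker as the dependent variable", with a separate model for each biomarker. "The initial model will simply include group as an explanatory factor". A further model adds confounders such as age and gives adjusted mean differences with 95% confidence intervals and tests, "comparing fracture patients with dementia to fracture patients without and fracture patients with dementia to stable dementia patients". The Sample size section fixes the groups: "Thus, we shall assemble data from 3 groups (hip fracture and dementia, hip fracture and non-dementia, stable and dementia), each with an expected 200 subjects".

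One diagnostic and one remedy are named: "In the event of the residuals for these models not appearing normally distributed, an appropriate transformation will be applied, such as a logarithmic transformation". Nothing is said about equality of spread, robust standard errors or group-specific variances. The opening of the Analysis section calls this a summary of a detailed statistical analysis plan, which is not shown.

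**The concern.** Equal group sizes protect the pooled-variance standard error when two groups are compared in a two-group model. They do not protect a two-group contrast taken from a three-group model, because the error term then includes the variance of the group left out.

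The design makes unequal spread plausible, although the article has no figures to show it:

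- Both fracture groups are sampled during an acute inflammatory response. The Background describes the Oslo comparison as being "with an existing cohort of patients living with dementia who have not experienced a systemic inflammatory response from an injury".
- Membership of the fracture-dementia group rests on a documented diagnosis or, failing that, an informant score of 3.31 or above (Design). Oslo patients have a confirmed diagnosis from a memory clinic (Sample size).
- Oslo samples were assayed in 2017 at one laboratory (Sample size). The study's own samples come from many hospitals and are to be analysed at three institutions (Secondary hypothesis).

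At stake are the interval and P value of either primary contrast. One may be too narrow and significant too often while the other is too wide and loses power.

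**Working it through.** **Inputs.** From the Sample size section: 200 per group, two-sided 5%, and "statistical power of 90% to detect a mean between group mean differences of 0.33 standard deviations in any outcome variable". From the Primary hypothesis section: one model per marker, a three-level group factor and two contrasts. Group SDs are not given, so a range is assumed.

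**The plan's own figure.** The standard error of a difference, in SD units, is √(2/200) = 0.10. Power at 0.33 SD is Φ(0.33/0.10 − 1.96) = Φ(1.34) = 91%, which agrees with the stated 90%. The difference detectable at exactly 90% is (1.960 + 1.282) × 0.10 = 0.324 SD. Dividing by √(1 − 0.25) gives 0.374, the stated adjusted figure of about 0.37. The sample size arithmetic is sound under a common variance.

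**Formulas.** Write D for fracture with dementia, N for fracture without dementia and O for Oslo, with SDs s_D, s_N and s_O and equal n.

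- Pooled variance used by the model: (s_D² + s_N² + s_O²)/3
- Variance needed for D−N: (s_D² + s_N²)/2
- Variance needed for D−O: (s_D² + s_O²)/2
- Ratio r of model to true standard error: √(pooled/needed)
- Actual two-sided type I error: 2 × [1 − Φ(1.96 r)]

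**Worked case, SDs (2, 2, 1).** Pooled = (4 + 4 + 1)/3 = 3. For D−N, needed = 4, r = √0.75 = 0.866 and type I error = 9.0%. For D−O, needed = 2.5, r = √1.2 = 1.095 and type I error = 3.2%.

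**Range of assumed SDs.**

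| SDs (D, N, O) | r, D−N | Type I error, D−N | r, D−O | Type I error, D−O |
|---|---|---|---|---|
| 1, 1, 1 | 1.00 | 5.0% | 1.00 | 5.0% |
| 1.1, 1.1, 1 | 0.97 | 5.7% | 1.02 | 4.7% |
| 1.25, 1.25, 1 | 0.94 | 6.6% | 1.04 | 4.2% |
| 1.5, 1.5, 1 | 0.90 | 7.7% | 1.06 | 3.7% |
| 2, 2, 1 | 0.87 | 9.0% | 1.10 | 3.2% |
| 2, 1.58, 1 | 0.88 | 8.6% | 1.00 | 5.0% |
| 1.5, 1, 0.67 | 0.87 | 8.8% | 0.96 | 6.1% |
| 1, 1, 2 | 1.41 | 0.6% | 0.89 | 8.0% |

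In the last row, power for D−N at 0.33 fracture-group SDs falls to Φ(3.30 − 1.96 × 1.414) = Φ(0.53) = 70%.

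**At least one contrast is off.** D−N is exact only if s_O² = (s_D² + s_N²)/2. D−O is exact only if s_N² = (s_D² + s_O²)/2. Subtracting the two conditions gives s_O² = s_N², and then all three variances are equal. Unequal variances therefore always disturb at least one contrast.

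**Simulation.** In 40,000 runs at SDs (2, 2, 1), the pooled model gave 8.8% for D−N and 3.1% for D−O. Welch contrasts, with contrast-specific variances, gave 4.9% and 5.1%. Over the five SD patterns simulated, Welch stayed between 4.9% and 5.1%. In a smaller simulation with an age covariate (2,000 runs, SDs 1, 1, 0.5), ordinary standard errors gave 8.7% and 2.8%, and HC3 gave 4.5% for both.

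**Would the normality check catch it?** Take SDs (1.5, 1.5, 1) with normal data in each group. The mean of s⁴ is (5.0625 + 5.0625 + 1)/3 = 3.708 and the squared mean of s² is 1.833² = 3.361. The excess kurtosis of the pooled residuals is 3 × 3.708/3.361 − 3 = 0.3, with no skewness. That could easily pass as normal while the D−N type I error is 7.7%.

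**The case against.** The strongest objection is scope. The article is a summary, and variance diagnostics and the choice of standard error are ordinary content for the analysis plan. The term general linear model does not exclude robust standard errors, and the Secondary hypothesis section promises the most appropriate analysis should new information arise. This stands to the extent that silence on equal spread is not itself an error, and the plan not shown may already deal with it. It does not remove the point, because the article states the model, the contrasts, the diagnostic and the remedy, and a plan that follows it literally inherits the problem.

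Second, a logarithm also tends to equalise variances when spread grows with the mean. That is true and may reduce the problem for many markers. But the transformation is triggered only by non-normality, and it does not equalise groups that differ in spread on the log scale.

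Third, the reach is limited. Of the nine markers in the Primary objective, TNF-α, IL-1β and IL-6 appear on the Oslo assay list in the Sample size section (neurogranin too, if G36-NG2 denotes it). Unless further Oslo assays are planned, the other models hold only the two fracture groups, where equal size makes the pooled standard error correct without covariates.

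A reader might infer that both contrasts are wrong whenever the spreads differ. The arithmetic does not support that: at SDs (2, 1.58, 1) the Oslo contrast is exact. Nor does a less variable Oslo group always make the Oslo contrast conservative. That holds when the fracture SDs are equal, but at (1.5, 1, 0.67) its type I error is 6.1%.

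**Conclusion.** The point holds in a limited form, for markers compared across all three groups. With a single residual variance, unequal spread on the analysis scale miscalibrates at least one of the two contrasts, and neither 200 per group nor the stated normality check and transformation reliably prevents it.

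The size rests on assumed SDs. With equal fracture SDs, ratios of 1.1 to 1.25 move type I error only to between 4.2% and 6.6%, while ratios of 1.5 to 2 give 7.7% to 9.0% for the fracture-fracture contrast. The drop to 70% power needs Oslo to be twice as variable as the fracture groups, the opposite of what acute inflammation of varying severity would suggest. Unequal achieved numbers change the figures: with 120, 200 and 200 patients and SDs (2, 2, 1), type I error is 9.8% for the fracture-fracture contrast and 5.1% for the Oslo contrast.

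Severity is minor to moderate. The article does not show that either primary result will be wrong.

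**What to change.** State in the analysis plan that both contrasts, unadjusted and adjusted and on whichever scale is analysed, use HC3 standard errors or a model with a separate residual variance per group. Make this the default rather than conditional on a test of equal variance or on the normality check.

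The cost is one sentence and one software option, with no extra data. If the variances are in fact equal, the loss of efficiency is negligible: with 200 per group, a contrast-specific variance has about 398 degrees of freedom instead of 597, and the critical value moves from 1.964 to 1.966.

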#### Secondary objectives

To determine whether the magnitude of the brain inflammatory response predicts the quantity of specific brain injury markers measured in the CSF. Magnitude of the brain injury will be assessed via brain injury markers T-tau, P-tau, NfL, neurogranin, synaptotagmin and SNAP-25 in CSF. We will also examine if patients who are Aβ-positive at baseline are more or less likely to have dementia or develop dementia at follow-up. We will also look for interactions of Aβ positivity with the other biomarkers in regards to clinical outcome.

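### The informant score that helps define dementia is then tested by dementia group, and the schedule shown cannot detect newly developed dementia

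*Protocol article*

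**What the plan says.** **Grouping.** Under Design (text after Fig. 1), the final group depends on the patient's notes and, where possible, an informant's IQCODE. For patients without a formal diagnosis on record, those with a "suitable informant IQCODE score of 3.31 and above will be assessed as having sufficient evidence of dementia". Participants adds that this proxy information concerns cognition before the fracture and serves group allocation. An informant is wanted but not required.

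**Testing.** Under Analysis, Primary hypothesis, the article says: "We also predict that patients with dementia will have significantly worse cognitive and functional informant-based scores". It then applies a similar analysis to the marker models (a general linear model by group, with confidence interval and significance test), with cognitive and functional scores as the dependent variable.

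**Instruments.** Table 1 lists one informant-completed score, the IQCODE. Being able and consenting to complete it is an informant inclusion criterion. The patient's own cognitive measures are the AMT/4AT and the MMSE-2:SV at about 48 hours, 60 hours at the latest. Table 1 names no functional scale.

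**Follow-up.** Secondary objectives plan to "examine if patients who are Aβ-positive at baseline are more or less likely to have dementia or develop dementia at follow-up". The last time point in Table 1 is 1 month ± 5 days. At that point the clinical team is to "assess if the patient has a pre-existing documented diagnosis of dementia" and to complete the IQCODE if still outstanding. Footnote c to Table 1 allows both to be obtained earlier. Under Sample size, a non-confused patient with evidence of dementia at 1 month moves to the dementia group.

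**The concern.** There are two separate faults, each with its own fix.

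1. A variable used to form the groups is compared between those groups as an outcome. A significant difference would partly restate the allocation rule. Because the prediction sits under the primary hypothesis, a very small p-value there carries little information but is presented beside results that do carry some.

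2. One objective concerns a new event, the development of dementia, while the data collection shown looks only for dementia that predates the fracture. The objective has no assessment to match it.

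**Working it through.** **Step 1: the plan's own figures.** Inputs from Sample size: 200 per group, two-sided 5%, 90% power for "mean differences of 0.33 standard deviations in any outcome variable", and about 0.37 residual SD after adjustment with R² up to 0.25.

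- Power = Φ(0.33 × √(200/2) − 1.96) = Φ(3.30 − 1.96) = Φ(1.34) = 0.910 (exact noncentral t: 0.909). The stated 90% reproduces.
- Difference detectable at exactly 90%: (1.960 + 1.282) × √(2/200) = 0.324 SD. Adjusted: 0.324/√0.75 = 0.374. The stated 0.37 reproduces.

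The sample size is not at issue. The 0.33 SD serves below only as a yardstick, in within-group SD.

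**Step 2: what the rule does to the scores.**

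| Patient | IQCODE value, if there is one |
|---|---|
| Non-dementia group | below 3.31 by construction |
| Dementia group, by IQCODE alone | 3.31 or above by construction |
| Dementia group, by documented diagnosis | any value |

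**Step 3: size if everyone is classified by IQCODE.** Assume a standard normal score with no information about dementia and a proportion p above the cut c. The documents do not give p, so a range is used. The group means are φ(c)/p above and −φ(c)/(1 − p) below.

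- p = 0.5: 0.3989/0.5 + 0.3989/0.5 = 1.60 total SD. Each truncated half has variance 1 − 0.798² = 0.363, so the within-group SD is 0.603 and the difference is 1.596/0.603 = 2.65 within-group SD.
- p = 0.3 or 0.7: 0.3477/0.3 + 0.3477/0.7 = 1.66 total SD. The two variances are 0.265 and 0.493, giving a pooled SD of 0.615 and a difference of 2.69 within-group SD.

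On the scale of the design target this is 2.65/0.33 = 8.0 to 2.69/0.33 = 8.2 times as large. Power with 200 scored per group is effectively 100%.

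**Step 4: size if some dementia cases enter through records.** Let a share f of the dementia group enter through the IQCODE and give the rest pure-noise scores. All scored controls lie below the cut. The difference in total SD is f × φ(c)/p + φ(c)/(1 − p).

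- Cut at the median: f = 0 gives 0.80; f = 0.25 gives 0.25 × 0.798 + 0.798 = 1.00; f = 0.5 gives 1.20. In 2,000 simulated trials per setting, with 200 or with 100 scored controls, the t-test rejected every time.
- 10% above the cut, f = 0: 0.1755/0.9 = 0.20 total SD. The control variance is 0.712, so the pooled SD is √((1 + 0.712)/2) = 0.925 and the difference is 0.21 within-group SD. Power = Φ(2.11 − 1.96) = 56%.
- 5% above the cut, f = 0: 0.1031/0.95 = 0.11 total SD, and power is about 21%.
- 10% above the cut, f = 0.25: 0.25 × 1.755 + 0.195 = 0.63 total SD, and power is again about 100%.

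**Step 5: new dementia.** The sources of dementia evidence are the records review and the IQCODE. The first seeks a pre-existing diagnosis and the second concerns pre-fracture cognition. Both may be completed before 1 month. The last cognitive test of the patient is no later than 60 hours after surgery. A non-confused patient with evidence at 1 month joins the dementia group. No step separates a new case from an existing one.

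**The case against.** **The test need not come out positive.** The IQCODE rule applies only without a documented diagnosis, and some patients will have no informant. If most dementia cases come through records and few scores exceed the cut, the artefact can be small (Step 4). This stands. A reader might infer that the test must be significant whatever the biology. The documents do not support that, because they give neither the share classified by IQCODE nor the proportion above 3.31.

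**Circularity might seem to reach the record evidence too.** It does not. Aβ status plays no part in grouping, so relating it to having dementia is sound. Only the words about developing dementia lack support.

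**Late-found dementia might seem to be relabelled as new onset.** The plan does the opposite for non-confused patients: it reallocates them to the dementia group. The fault is a missing assessment, not a planned misclassification.

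**The score test is ancillary.** This is correct. The primary hypothesis is addressed through CSF and blood markers. That the score result would be taken as support for it is conjecture.

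**Functional scores may be collected elsewhere.** The 1-month section mentions additional clinical measures and test results without itemising them. Absence from Table 1 therefore does not prove that no functional measure exists.

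**The 48-hour MMSE-2:SV looks like a clean substitute.** It does not define dementia, but it is not free of selection. Controls drawn from Group 2 were required to have an AMTS of 9 or above or a 4AT of 0, and confused patients without dementia evidence go to the biobank. Part of any MMSE contrast is built in as well.

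**Conclusion.** Both faults hold on the text shown, and both are limited in scope.

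The IQCODE is not an independent outcome for groups that it helps to define. With pure-noise normal scores the artefact is about 2.65 to 2.7 within-group SD if all patients are classified by IQCODE with 30% to 70% above the cut. It is about 0.8 total SD if all dementia cases enter through records with the cut at the median, and about 0.2 SD if only 10% of scores exceed it. These sizes are illustrations. The structural fault does not depend on them, since scored controls lie below 3.31 in every case. Setting the 1.6 total SD directly against the 0.33 SD target would mix scales and understate the ratio.

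The question of who develops dementia cannot be answered on the schedule shown.

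The primary CSF comparisons, the sample size and the analysis of Aβ status against prevalent dementia are unaffected. The point should be corrected, but it does not threaten the main analysis.

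**What to change.** **Analysis, Primary hypothesis.** Remove the significance test on the IQCODE and report it by group descriptively, as a check of classification. Remove the functional-score test unless a functional measure not used for grouping is actually collected, and name that measure if so. If the MMSE-2:SV is compared, state that controls were selected on AMTS/4AT and that confused patients without dementia evidence are left out.

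**Secondary objectives.** Limit the Aβ objective to prevalent dementia, or name an assessment and time point already available that can detect new dementia.

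**Cost.** Wording only. One uninformative test is lost and one objective becomes narrower. No sample, visit or power figure changes.
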